## Gait and balance

Gait endurance will be measured using the 6-min walk test which has excellent test-retest reliability (ICC = 0.96) and established minimal detectable change values in this population [31]. Functional mobility and balance will be measured using the Timed up and go (TUG) test with and without added dual tasks [32]. Gait speed and step length will be measured with and without added dual tasks using the 8m instrumented GAITrite™ walkway and existing testing protocols [33].

## Quality of life

Health-related quality of life will be measured using the 39-item Parkinson’s disease questionnaire—PDQ-39 [34]. It will be collected at all three time points with an interviewer present to clarify questions or assist with writing if required.

## Participant characteristics

Participant characteristics collected at baseline will include demographic data (age, sex, years since diagnosis), medical history and general health status. To characterize their Parkinson’s disease, at every time point severity of PD will be rated using the Hoehn & Yahr Stage [35]; levodopa equivalent dose will be calculated from their prescribed medication; and the Movement Disorders Society MDS-Unified Parkinson’s disease rating scale motor subsection III [36] and the Freezing of Gait questionnaire [37] will be completed. Exercise self-efficacy will be measured at post and follow-up assessments using the Outcome Expectations for Exercise (OEE) Scale [38] and the Self-efficacy for Exercise Scale (SEEs) [39].

The occurrence and details of any adverse events (e.g. falls), experienced since the last assessment session, will be recorded at the post intervention and follow-up assessments.

### Plans to promote participant retention and complete follow-up {18b}

All data will be managed with an intention to treat philosophy, including any who deviate from the allocated intervention. Once participants are enrolled in the study, the research team will make every reasonable effort to follow them for the entire study period, including reminding them of upcoming data collection appointments. Participant retention through to follow-up will be optimized by regular contact throughout the intervention and follow-up period for those in the intervention group. Participants in the control group will be contacted between time points to schedule appointments and provide reminders. Any deviations from the study protocol and the trial’s time plan (including withdrawal) or from the intervention will be documented.

### Data management {19}

Following each assessment, data will be entered into a computer spreadsheet saved on a protected computer server within the university. Accuracy of data entry will be audited twice yearly by people external to the research team. Paper-based data files will be secured in a lockable cabinet in the locked office of the research team. All data will be retained for 15 years after completion of the research, to comply with Australian Government legislation.

### Confidentiality {27}

All written data will be maintained in a locked filing cabinet in the locked office of one of the chief investigators. Electronic data will be stored on a password-protected computer.

### Plans for collection, laboratory evaluation and storage of biological specimens for genetic or molecular analysis in this trial/future use {33}

As seen in the “Additional consent provision for collection and use of participant data and biological specimens {26b}” section above, no biological specimens will be collected as part of this trial.

## Statistical methods

### Statistical methods for primary and secondary outcomes {20A}

To determine if there are differences between groups in physical activity outcomes post intervention, linear mixed models will be performed investigating group (intervention vs. control), time (baseline, post, follow-up) and group × time interactions for all variables. Baseline participant characteristics will be compared between groups and those with any differences included as covariates. Post hoc univariate testing will be undertaken if main effects and interactions are significant.

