### Trial design {8}

This study is a two-arm, parallel group, assessor-blinded randomized controlled superiority trial. Randomization will be performed in variable block permutations by an offsite person independent to the study with a 1:1 allocation ratio.

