### Outcomes {12}

The primary outcome measure is free-living physical activity (average number of steps per day) at post intervention (T2) assessment collected via an activity monitor (activPAL™) that will be worn for seven complete 24-h periods.

Secondary outcomes will include (a) free-living physical activity (average number of steps per day) at follow-up (T3); (b) additional measures of free-living physical activity (average daily time spent walking, average daily time spent sedentary) at each assessment time point; (c) gait endurance measured via the 6-min walk test at each assessment time point; (d) spatiotemporal gait parameters (step length, gait speed) during single and dual task conditions over 8 m using a GAITrite™ electronic walkway at each assessment time point; and (e) health-related quality of life (QOL) at each assessment time point; will be measured using the 39-item Parkinson’s disease questionnaire (PDQ-39).

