## Assignment of interventions: allocation

### Sequence generation {16a}

Computerized random numbers were generated in variable block permutations of 4 or 6 using Matlab™.

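### Covariates are chosen by chance baseline imbalance, and baseline steps/day enters as a response with free arm means, so pre-specification and precision are lost

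*Protocol article*

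**What the plan says.** The rule stands in the protocol article under Statistical methods for primary and secondary outcomes {20A}: "Baseline participant characteristics will be compared between groups and those with any differences included as covariates". No test, threshold or list of candidates goes with it.

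The same section fits mixed models with a group term plus "time (baseline, post, follow-up) and group × time interactions for all variables". Baseline is thus one of the response occasions, and nothing says that the arms share a baseline mean. Follow-up univariate tests come after significant model effects.

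Outcomes {12} places the decisive comparison at one visit: "The primary outcome measure is free-living physical activity (average number of steps per day) at post intervention (T2) assessment".

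The Participant characteristics section lists "demographic data (age, sex, years since diagnosis), medical history and general health status". It adds Hoehn & Yahr stage, levodopa equivalent dose, the MDS-UPDRS motor section and the Freezing of Gait questionnaire. Randomisation is "with a 1:1 allocation ratio" in "variable block permutations of 4 or 6", with no stratification factor named.

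**The concern.** Under sound randomisation, a baseline difference between arms reflects chance. Comparing the arms to find one says nothing about whether the variable predicts steps/day. A covariate improves a treatment estimate through its relation to the outcome, so a rule based on imbalance can admit irrelevant variables and pass over strong predictors that happen to be balanced. Without a criterion, two analysts could reach different covariate sets from the same data.

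The second issue is how the baseline value of the primary outcome is used. It is likely to be among the best predictors of T2 steps/day. Treating it as a response, with arm means free to differ, subtracts it in full instead of weighting it by its correlation with T2. At stake are precision on the primary outcome and the ability to say in advance which estimate decides the trial.

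**Working it through.** **The plan's own figure.** The plan gives no number for its covariate rule. The sample size is used here only for scale: 41 × 1.12 = 45.92, rounded to 46 per group and 92 in total, as stated. The 41 cannot be rebuilt, because SD, alpha, sidedness and power are not given.

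**Step 1: how often chance would change the covariate set.** The Participant characteristics section yields about nine or ten candidates. If a difference meant p < 0.05 and the candidates were independent (both assumptions), the chance of selecting at least one is 1 − 0.95^k: 23% for k = 5, 34% for 8, 37% for 9, 40% for 10 and 46% for 12.

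**Step 2: what an added covariate does to the T2 effect.** Write the model as Y(t) = time(t) + b·G + g(t)·G + c·Z + error, with Z fixed over time. Subtracting T1 from T2 gives Y(T2) − Y(T1) = [time(T2) − time(T1)] + [g(T2) − g(T1)]·G + error. The c·Z term drops out. A numerical check used 41 per group, complete data and a covariate imbalanced by 0.5 SD. The interaction estimate was 0.4770 (SE 0.2039) both with and without the covariate. With 12% dropout from 46 per group, the estimate moved by only about 0.01 to 0.02 SD. The group main effect and a separate T2 comparison do move.

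**Step 3: error rate and power under a fixed threshold.** A simulation used 41 per group, 8,000 runs, selection at p < 0.05, and 10 candidates of which two were prognostic. Baseline steps were also open to selection. Selected covariates could act on the change score, which is more than a main effect can do. Chance altered the covariate set in 42–43% of runs. Type I error under the rule was 0.044 to 0.048 against 0.05. Power at a true effect of 0.45 SD was:

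| rho | change score, no covariates | change score with the rule | baseline-adjusted |
|---|---|---|---|
| 0.5 | 53% | 52% | 64% |
| 0.7 | 73% | 73% | 80% |
| 0.8 | 89% | 88% | 92% |

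**Step 4: variance of the T2 effect.** Assume equal variance σ² at T1 and T2, and correlation rho between them.

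- Change-score contrast: variance per participant 2(1 − rho)σ².
- Baseline-adjusted: (1 − rho²)σ² = (1 − rho)(1 + rho)σ².
- Ratio: 2/(1 + rho).

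For a power scale, assume that 41 per group came from a two-sided 5% two-sample comparison with 80% power. Then d = (1.960 + 0.842) × √(2/41) = 0.619. A 22% increase would imply a coefficient of variation of 0.22/0.619 = 0.36.

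| rho (assumed) | variance ratio | power, change score | power, baseline-adjusted |
|---|---|---|---|
| 0.3 | 1.54 | 65.8% | 83.6% |
| 0.5 | 1.33 | 80.0% | 89.9% |
| 0.6 | 1.25 | 87.9% | 93.8% |
| 0.7 | 1.18 | 95.1% | 97.5% |
| 0.8 | 1.11 | 99.3% | 99.7% |

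At rho = 0.9 the ratio is 1.05.

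**The case against.** The strongest reply is that little of this touches the main contrast. Group, time and group × time are fixed in advance, and Step 2 shows that main-effect covariates leave the interaction unchanged with complete data. A mixed model with baseline as a response is valid and unbiased. Who will be blinded {17a} has the analyst blinded to allocation, which limits choosing covariates to favour an arm. All of that stands. What remains is that the rule has no benefit where it is harmless, and adds a chance-driven adjustment where it acts. Blinding does not fix the covariate list in advance.

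Three stronger readings are tempting, and the documents do not support them.

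- **Inflated type I error.** A reader might infer this from data-driven selection. Under one fixed threshold the simulation shows none. In a separate simulation of the T2 comparison, keeping the best result from thresholds of 0.05, 0.10, 0.20 and no covariates gave 0.064 to 0.072. That describes a search which the plan does not propose.
- **T1 steps/day as both response and covariate.** This could follow if steps/day counted as a participant characteristic. The article lists characteristics separately from outcomes, so the reading is strained.
- **A gain measured against an unadjusted T2 comparison.** That would look much larger, but the planned mixed model already uses baseline.

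It is also fair that the percentages in Step 1 rest on an assumed 5% test and on independence. Several of the disease-severity measures are plausibly correlated.

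**Conclusion.** The point holds as a should-fix. The covariate rule is stated explicitly, so it is not a detail left to an analysis plan. It selects on chance imbalance, has no criterion, and buys no precision. Its harm is lost pre-specification and the lost chance to adjust for prognostic variables.

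The treatment of baseline steps/day is a separate matter of efficiency. It costs 11% to 33% extra variance for rho between 0.8 and 0.5, under equal variances and complete data. The document gives no correlation: the cost would be larger below 0.5 and is small at 0.8 or above. The power figures also rest on an effect size back-solved from assumed alpha and power, so they show scale only.

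**What to change.** Delete the baseline-comparison rule, and report baseline characteristics descriptively, without tests.

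Name the primary estimate as the between-group difference in steps/day at T2. Take it from one of two models, chosen now: a mixed model with T1, T2 and T3 as responses and a common baseline mean for both arms, or one with T2 and T3 as responses and T1 steps/day as covariate.

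If further covariates are wanted, name a short list before unblinding, from variables already collected and chosen for expected prognostic value.

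The cost is one paragraph of analysis wording; no new data or participants are needed. The small downside is that an unlisted chance imbalance goes unadjusted in the primary model. A sensitivity analysis can show its effect.

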## Introduction

### Background and rationale {6a}

Despite pharmacological intervention, people with Parkinson’s disease (PD) show a steady decline in physical functioning due to cumulative deficits in motor and non-motor impairments. Physical activity is important to maintain in people with PD, as it not only contributes to maintaining functions such as gait, balance in standing, and muscle strength, but these contribute to safe performance of activities of daily living and maintenance of independence. One area of decline is in physical activity. Levels of physical activity are lower in people with PD than healthy controls [1–3] and have been shown to decline overtime without intervention [4].

While a Cochrane review has found that exercise-based interventions can lead to short-term improvements in gait and function in people with PD [5], longer-term changes are difficult to achieve [6]. Physical activity behaviour is complex and multifactorial. Identified barriers to physical activity in people with PD include exercise self-efficacy and fear of falling [7]. Qualitative findings indicate that feedback and motivation influence decision making with regards to exercise participation in people with PD [8]. The largest study of intervention to improve physical activity in PD used personalized motivational coaching alone which was no more effective at increasing self-reported physical activity in sedentary people with PD than advice promoting safe movement [9]. Post hoc analysis however revealed that those participants with greater levels of physical fitness and better walking ability demonstrated greater increases in physical activity than the control group [10]. Intervention to improve levels of physical fitness and walking ability may therefore be an important component of promoting physical activity behaviour change in this population.

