### Sample size {14}

The required sample size has been determined to be 92 participants (46/group) to detect a 22% increase in the number of steps/day immediately following the 4-week intervention. The proportion of change is based on previous studies of people with mild-moderate idiopathic PD who volunteered for exercise trials [1]. This determined a need for 41 participants per group. A conservative 12% allowance for withdrawals was included based on previous exercise trials in people with Parkinson’s disease [9]. Sample size was calculated using SPSS.

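### The primary T2 comparison of steps/day is not named in the analysis and sits behind omnibus tests over three visits, two of which do not test the hypothesis

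*Protocol article*

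**What the plan says.** The Outcomes section (item 12) is specific about the time point: "The primary outcome measure is free-living physical activity (average number of steps per day) at post intervention (T2) assessment". Steps/day at T3 is listed there as the first secondary outcome. The Sample size section (item 14) uses the same visit, sizing the trial "to detect a 22% increase in the number of steps/day immediately following the 4-week intervention" and adding: "This determined a need for 41 participants per group". An allowance for withdrawals brings this to 46 per group.

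The statistical methods section (item 20A) opens with the aim of finding group differences in physical activity after the intervention. The procedure it gives is that "linear mixed models will be performed investigating group (intervention vs. control), time (baseline, post, follow-up) and group × time interactions for all variables". It then sets the condition: "Post hoc univariate testing will be undertaken if main effects and interactions are significant". It makes no exception for the primary outcome, and no other section of the article lifts the condition.

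**The concern.** The trial has one primary question: do the arms differ in steps/day at T2? The analysis reaches that question only after omnibus tests, and neither main effect addresses it.

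- **Group main effect.** It averages the arm difference over three visits. At baseline, randomisation makes the expected difference zero, so that visit only dilutes. At T3 the difference is a secondary outcome and may have faded.
- **Time main effect.** It averages over the arms, so it is not a between-group comparison.
- **Interaction.** It is the relevant omnibus effect, but it has 2 df and mixes T2 with T3. Whether T2 is followed up then depends partly on a secondary visit.

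Two things are at stake. A true T2 effect of the planned size could go without its own test. And because the sentence can be read in more than one way, the choice of reading could be made after the omnibus results are known.

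**Working it through.** **The plan's own figure.** 41 × 1.12 = 45.9, rounded to 46 per group and 92 in total, which matches the article. (Dividing instead, 41/0.88 = 46.6, gives 47 per group; the difference is immaterial here.) The 41 itself cannot be reproduced, because the article states no SD, alpha, power or correlation.

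**Assumptions.** Two-sided 5%; 41 per arm with complete data; compound symmetry with correlation ρ of 0.5, 0.7 or 0.8; no time trend in controls; T3 effect equal to 100%, 50% or 0% of the T2 effect (fraction f). A two-sample t-test with 41 per arm has 80% power at d = 0.626: the noncentrality is 0.626 × √(41/2) = 2.83. If the 22% is a between-group difference, this implies an SD of about 22/0.626 = 35% of the baseline mean.

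**Group main effect, by hand at ρ = 0.7.** The mean of three visits has variance (1 + 2ρ)/3 = (1 + 1.4)/3 = 0.80, so its SD is 0.894. The mean arm difference is 0.626(1 + f)/3. The standardised effect is:

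- f = 1: 0.417/0.894 = 0.47, power about 55%
- f = 0.5: 0.313/0.894 = 0.35, power about 35%
- f = 0: 0.209/0.894 = 0.23, power about 18%

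**Interaction, by hand at ρ = 0.7.** The noncentrality is λ = (n/2) Σ(δₜ − δ̄)²/(1 − ρ) on 2 and 160 df, where δₜ is the arm difference at visit t.

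- f = 1: λ = 20.5 × 0.2612/0.3 = 17.9, power 97%
- f = 0.5: λ = 20.5 × 0.1959/0.3 = 13.4, power 91%
- f = 0: same λ as f = 1, power 97%

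**Joint behaviour, by simulation.** 20,000 trials per row, with split-plot F tests (the complete-data equivalent of the mixed model). Entries are percentages.

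| ρ | f | Group | Time | Interaction | All three | Any one | T2 unadjusted: direct → behind interaction | T2 baseline-adjusted: direct → behind interaction |
|---|---|---|---|---|---|---|---|---|
| 0.5 | 1 | 63 | 83 | 83 | 44 | 99 | 80 → 69 | 90 → 78 |
| 0.5 | 0.5 | 40 | 71 | 71 | 20 | 95 | 80 → 61 | 89 → 70 |
| 0.5 | 0 | 21 | 84 | 84 | 15 | 98 | 80 → 72 | 89 → 80 |
| 0.7 | 1 | 55 | 97 | 97 | 52 | 99.9 | 80 → 79 | 97 → 95 |
| 0.7 | 0.5 | 35 | 91 | 91 | 29 | 99 | 80 → 75 | 97 → 91 |
| 0.7 | 0 | 18 | 97 | 97 | 17 | 100 | 80 → 79 | 97 → 96 |
| 0.8 | 1 | 52 | 99.8 | 99.8 | 51 | 100 | 80 → 80 | 99.6 → 99.4 |
| 0.8 | 0.5 | 33 | 98 | 98 | 32 | 100 | 80 → 79 | 99.6 → 98 |
| 0.8 | 0 | 17 | 99.7 | 99.8 | 17 | 100 | 80 → 80 | 99.6 → 99.4 |

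The group main effect is the bottleneck on the literal reading, and it is worst when the effect fades by T3.

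**Other sizing bases.** If 41 per arm was instead derived from change scores at 80% power, the literal gate opens in 7–43% of trials, the interaction gate in 71–84% and the any-effect gate in 93–100%. If the trial was sized for 90% power (d = 0.725, on either basis), the literal gate opens in 10–67%.

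**The case against.** The strongest reply is that the sentence is common shorthand for following up whichever effects prove significant, in a paragraph that covers all variables and opens by aiming at post-intervention group differences. On that reading the interaction is what matters, or any effect will do, and the table shows that the loss can then be negligible. This stands as a limit on the size of the problem. It does not remove it: the literal wording joins the effects with *and*, no T2 contrast is named, and the interaction gate still costs 10 to 20 points of baseline-adjusted power at a correlation of 0.5.

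Several stronger readings are tempting and not supported:

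- **That the primary comparison would never be reported.** The condition governs post hoc testing, not reporting. The model is fitted unconditionally, and its group × time terms carry the T2 difference in change from baseline.
- **That the post hoc test discards baseline.** The article does not define that test; it could be a contrast from the model, which includes the baseline visit.
- **That the loss is 97% power against 17–52%.** This compares a baseline-adjusted direct test with the three-effect gate, so it mixes the gain from adjustment with the loss from gating.
- **That the gate would almost never open because controls decline as the intervention arm rises.** Opposite movements would indeed cancel in the time effect, and the Background section says activity levels "have been shown to decline overtime without intervention". But it gives no rate or period, and nothing supports a large fall in controls by T2.

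It is also fair that alpha, the exact contrast and interval wording are often left to an analysis plan, which is not shown. Their absence is not the point here. The point is a rule that the article does state.

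**Conclusion.** The point holds as a badly fixed rule for the primary analysis. The primary outcome and the sample size concern the between-group difference at T2, while the methods section makes time-specific testing depend on effects that dilute that difference or do not measure it.

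The size is a range. At 80% sizing on an unadjusted T2 test and correlations of 0.5 to 0.8, the gate opens in about 15–52% of trials if all three effects are required, 71–99.8% if only the interaction gates, and 95–100% if any one effect suffices. Behind the interaction gate, unadjusted T2 power falls from 80% to about 61–80%, and baseline-adjusted power from about 90–99.7% to 69–99.5%. These figures rest on assumed alpha, power, effect size, correlation structure and T3 persistence. A reader might infer that the trial will probably miss its planned effect. That follows only from the strictest reading, and the documents do not settle which reading is meant.

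**What to change.** For the primary outcome, replace the gating sentence with:

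> *The primary analysis is the intervention-minus-control difference in steps/day at T2, estimated from the mixed model using the baseline value, tested with 1 df at two-sided 5% and reported with its 95% CI, whatever the main effects or the interaction show.*

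Name the T3 difference as a secondary contrast from the same model. The omnibus interaction can stay as a supporting result.

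The cost is wording only. The Trial status section says recruitment was still open, so the change could be made before unblinding, through the amendment route the article describes (management committee, ethics committees, funder, registry). If an analysis plan already specifies a direct T2 contrast, the article's sentence should be reconciled with it.
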